### Data analysis

We will follow intention-to-treat principles at both individual and cluster levels. Participants will be assigned to the cluster they were in when the trial began. However, if a participant moves to another cluster during the trial period that is assigned to a higher intervention arm, they will be shifted to that cluster.

In data analysis, we will first analyse descriptive variables to explore the distribution of background data using chi-square and *t*-tests. To compare intervention effects between control and intervention groups, we will use adjusted, generalised linear models and modified *t*-tests, taking into account the effect size. Analyses will be conducted at the cluster and individual level, and all estimates will be presented with standard deviations or 95% confidence intervals.

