### Trial design

After developing the TDQ, we will conduct a provider baseline survey and EDR audit to measure the baseline adherence to TUPAC counselling guidelines and prevailing implementation difficulties among our sample. Based on identified implementation difficulties, we will use relevant behaviour-change theories and techniques in designing two interventions to enhance TUPAC guideline implementation. In selecting relevant intervention techniques, we will use a matrix of theoretical domains and 35 behaviour-change techniques [19] (Figure 1). Finally, we will test these interventions using a cluster randomised controlled trial (Figure 2).

Dental providers usually work in only one clinic, but when this is not the case, chief dental officers will merge two or more clinics into one cluster to reduce contamination across participants. After merging clinics and forming clusters, chief dentists will provide a concealed sequence of clusters to investigators who will allocate clusters randomly to (a) control, (b) low-intensity intervention, or (c) high-intensity intervention groups (Figure 2) by drawing lots. Allocation will be concealed from the investigators until data collection has been conducted. Investigators, patients, outcome assessors, and study statistician will be blinded to group allocation until the statistical analysis has been completed. Due to the nature of the study setting, it is not possible to blind the dental providers for group allocation. The success of blinding will not be evaluated.

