### Sample size

There is a scarcity of recent national data regarding the implementation of TUPAC counselling guidelines reported by dental providers. Hence, we conducted our sample size calculations based on population reports collected by the National Institute for Health and Welfare from a random sample (n = 5,000) of Finnish adults [8]. The data showed that 10.5% of surveyed tobacco users who visited the dentist at least once during the past 12 months had received any TUPAC counselling [8]. As our primary aim is to compare the implementation of TUPAC counselling guidelines between control versus two intervention groups, sample size is calculated using the following assumptions: Our aim is to increase the proportion of counselled patients from 10.5% (control) to 33% in the first (low-intensity) intervention group and to 63% in the second (high-intensity) intervention group, as validated by dental record audit. To achieve 80% power, with a two-sided 5% significance level with an estimated intra-class correlation of 0.02, we will need totally 72 participants and 12 clusters with an average of six participants per cluster. Assuming a baseline response rate of 76%, we will need a sample of 95 dental providers.

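### Shifting participants who move to a higher-arm cluster contradicts the stated intention-to-treat principle and can bias both comparisons with control, in either direction

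*Protocol article*

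**What the plan says.** The first paragraph of Data analysis in the protocol article makes three consecutive statements:

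- The principle: "We will follow intention-to-treat principles at both individual and cluster levels".
- The default: "Participants will be assigned to the cluster they were in when the trial began".
- The exception: "if a participant moves to another cluster during the trial period that is assigned to a higher intervention arm, they will be shifted". The destination is the new cluster.

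The exception is not labelled a sensitivity or per-protocol analysis. No matching rule covers a move to a lower arm, so a downward mover stays under the default.

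Trial design sets out the three arms, in which investigators "allocate clusters randomly to (a) control, (b) low-intensity intervention, or (c) high-intensity intervention groups". It says of the providers that "it is not possible to blind the dental providers for group allocation", and that the "study statistician will be blinded to group allocation until the statistical analysis has been completed". The same blinding applies to investigators, patients and outcome assessors. It also says that most providers are attached to one clinic, and that clinics sharing staff are merged into one cluster before randomisation.

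Under Sample size, "our primary aim is to compare the implementation of TUPAC counselling guidelines between control versus two intervention groups".

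**The concern.** Intention-to-treat at the individual level means that a participant's arm is fixed by randomisation and that nothing afterwards changes it. The exception changes it for one class of participant, according to where they work later.

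The rule runs one way. Control can only lose people, high-intensity can only gain them, and low-intensity gains from control and loses to high-intensity. The arms compared are therefore no longer the arms that were randomised, and both contrasts with control are exposed. Providers know their allocation, so a move could be related to it. With about 24 providers per arm, two movers are 2/24 = 8.3% of an arm, so a few people could matter.

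There is also a practical difficulty. Whoever applies the rule must know which cluster is in the higher arm, while investigators and statistician are meant not to know this until the analysis is complete.

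**Working it through.** **The text.** The principle and the default give one answer for a control provider who moves to a high-intensity clinic: control. The exception gives another: high-intensity. Both cannot hold in the same analysis. This step needs no figure.

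**Size under no true effect.** The plan has no figure of its own for movers, so this is an illustration.

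Inputs from the Sample size section: 72 participants and a control rate of 10.5%.

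Assumptions: equal allocation (the ratio is not stated), so 72/3 = 24 per arm; every arm truly at 10.5% as randomised; two control providers move to high-intensity; these two counsel at rate *q*.

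Each arm as randomised sums to 24 × 0.105 = 2.52. After the shift:

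- control = (2.52 − 2*q*)/22
- low-intensity = 0.105, unchanged
- high-intensity = (2.52 + 2*q*)/26

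| Movers' rate *q* | Control | Low | High | Low − control | High − control |
|---|---|---|---|---|---|
| 0% | 2.52/22 = 11.45% | 10.5% | 2.52/26 = 9.69% | about −1.0 | about −1.8 |
| 10.5% (typical) | 2.31/22 = 10.5% | 10.5% | 2.73/26 = 10.5% | 0 | 0 |
| 40% | 1.72/22 = 7.82% | 10.5% | 3.32/26 = 12.77% | about +2.7 | about +5.0 |

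Differences are in percentage points. Analysed by original cluster, all three arms stay at 10.5% and every difference is zero.

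**Size if the interventions work as planned.** The planned differences from control are 33 − 10.5 = 22.5 and 63 − 10.5 = 52.5 points. Assume 12 clusters of six, four per arm. Each provider moves with probability *p* to one of the other 11 clusters at random. Movers are otherwise typical and show the new cluster's effect for the whole period.

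By original cluster, the chance of being located in one's own arm is 1 − 8*p*/11, and the chance of being in any given other arm is 4*p*/11. Each planned difference is therefore multiplied by (1 − 8*p*/11) − 4*p*/11 = 1 − 12*p*/11.

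- *p* = 0.083: factor 0.909, giving 20.5 and 47.7 points.
- *p* = 0.167: factor 0.818, giving 18.4 and 42.9 points.

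A simulation of the same set-up (20,000 runs per scenario) agrees for the original-cluster analysis and gives the shift-rule results:

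| *p* | Low − control: original cluster / shift rule | High − control: original cluster / shift rule |
|---|---|---|
| 8.3% | 20.4 / 21.8 | 47.7 / 50.1 |
| 16.7% | 18.4 / 21.1 | 42.9 / 48.0 |

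So even with typical movers the rule departs from the intention-to-treat contrast once there is an effect: by 1.4 and 2.4 points at 8.3%, and by 2.7 and 5.1 points at 16.7%.

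**Scale.** These figures are proportions counselled, as used for the sample size. The primary outcome is a continuous score of procedure codes weighted by odds ratios. The mechanism carries over, but the point values do not translate directly.

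**The case against.** The strongest defence is that the rule may hardly ever operate. Merging clinics that share staff before randomisation deals with regular cross-clinic work and leaves mainly actual changes of workplace, which may be few. If nobody moves upward, the rule changes nothing. If there is no effect and movers resemble the others, it changes nothing on average. This stands as a limit on the likely size. It does not reconcile the sentences, and the authors evidently thought moves likely enough to write a rule for them.

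A second defence is that leaving movers where they started weakens the contrast. That is true and not trivial: under the assumptions above, 8.3% movers cost 52.5 − 47.7 = 4.8 points in the high-intensity comparison. It is the known price of the principle the plan adopts.

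A reader might infer more than the article supports:

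- That the rule does bias both comparisons, in favour of the interventions. The article says nothing about how many people move or who they are, and low-counselling movers push the result the other way.
- That this is an as-treated analysis. It is not, because downward movers are not reassigned. It is a one-directional hybrid.
- That 5 points is an estimate of the bias. It is one end of an assumed range.

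**Conclusion.** The contradiction is established from the text alone: the plan states intention-to-treat at both levels and then reassigns upward movers on a post-randomisation event, in what reads as the main analysis. Nothing elsewhere in the article corrects it.

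The bias is conditional. It can affect both comparisons with control, and its sign and size are unknown. The illustrative range for high-intensity minus control, about −1.8 to +5.0 points, rests on equal arms of 24, no true effect, exactly two control-to-high moves and mover rates between 0% and 40%. Only the 72 participants and the 10.5% come from the article. The planned differences are 22.5 and 52.5 points, so the case for correction rests on the broken principle and not on these magnitudes.

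The tension with blinding is secondary. Someone outside the blinded group could apply the rule, but the article names no such person.

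**What to change.** Delete the sentence that moves participants to the new cluster. State that every participant is analysed in the cluster, and so the arm, held at randomisation, whatever moves follow in either direction. If counselling after a move is of interest, report an analysis by actual location as a labelled sensitivity analysis, with the number and direction of moves by arm, run once the blinded analysis is complete.

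The cost is one sentence. No further data are needed, because the shift rule itself already requires movers' records from the new clinic. The downside is dilution if the interventions work. Under the assumptions above, 8.3% movers reduce the planned 22.5 and 52.5 points to about 20.4 and 47.7, and 16.7% movers reduce them to about 18.4 and 42.9.

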### Primary outcome measures

The meta-analysis shows that if TUPAC guidelines are implemented, the time used by healthcare providers for counselling is one of the best predictors for counselling success [13]. As our target behaviour will be the implementation of TUPAC guidelines, our primary outcome measures will be (a) whether the TUPAC guideline recommendations are implemented, and (b) if implemented, the estimated time used for the counselling. We will use the electronic dental record (EDR) audit for measuring these outcomes. If the dentist or dental hygienist provides TUPAC counselling, documented procedure codes will give information on the effect counselling may have had. A similar procedure-code documenting system is widely used in dentistry (fillings, extractions, etc.). The codes for TUPAC counselling will be as follows: TI02 = minimal counselling (<3 minutes), TI03 = low-intensity counselling (3 to 10 minutes), and TI04 = higher-intensity counselling (>10 minutes). Categories of intervention duration are based on the meta-analysis, where the estimated odds ratios (ORs) for TUPAC counselling are reported using the same counselling durations (OR = 1.3 for minimal counselling, OR = 1.6 for low-intensity counselling, and OR = 2.3 for higher-intensity counselling) [13]. When multiplying the procedure codes by the estimated ORs and summing the results, we will create one continuous primary outcome. The EDR softwares used in the Vaasa and Tampere health centres are identical (Effica by Tieto Finland, Helsinki) and include the above-mentioned codes for each intervention intensity.

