### Trial update

The baseline survey (background information, self-reported guideline implementation, the theory-based assessment of implementation difficulties) and the EDR audit of the sample were conducted in September 2009. Of those eligible, 76.8% participated (n = 73/95). The study participants were fairly representative of municipal dental providers (Table 1). Participating dentists had practiced more clinical years on average (22.4 years) compared to dental hygienists (10.2 years; *p *< .001) and reported higher lifetime tobacco abstinence (72.2%) than dental hygienists (21.1%; *p *< .001) (Table 2). Regular tobacco use was uncommon in both provider groups. More dental hygienists had received undergraduate education on TUPAC counselling compared to dentists (84.2% versus 24.1%; *p *< .001). The results of the self-reported guideline implementation, theory-based assessment of implementation difficulties, and EDR audit will be reported elsewhere.

**Table 1 T1:** The comparison of gender and mean age of study participants, nonrespondents, and municipal dental practitioners in Finland

	Participants		Nonrespondents		Total		Municipal dentists
	Dentists (n = 54)	Hygienists (n = 19)	Dentists (n = 19)	Hygienists (n = 3)	Dentists (n = 73)	Hygienists (n = 22)	Dentists* (n = 2,002)
Female (%)	81.5	100	68.4	100	78.1	100	77.4
Mean age, years (SD)	48.7 (9.1)	37.3 (9.5)	51.1 (9.3)	46.7 (16.7)	48.9 (9.5)	38.6 (10.7)	49.5 (8.7)

*Finnish Dental Association statistics 2010. No national data available for dental hygienists.

**Table 2 T2:** Participant characteristics at baseline

	Dentists (n = 54)	Dental hygienists (n = 19)	*p *value*	Total (n = 73)
Response rate (%)	74.0	86.4	.27	76.8
Years practised (SD)	22.4 (9.1)	10.2 (7.6)	<.001	19.2 (10.2)
Mean clinical hours per week (SD)	28.0 (7.4)	31.1 (8.2.)	.14	28.8 (7.7)
Tobacco use (%)				
Never	72.2	21.1	<.001	58.9
Gave up 1 to 12 months ago	3.7	0	.40	2.7
Occasional	1.9	10.5	.10	4.1
Regular	3.7	5.3	.71	4.1
Received undergraduate education on tobacco use prevention or cessation counselling (%)	24.1	84.2	<.001	39.7
Received continuing education on tobacco use prevention or cessation counselling (%)	37.0	31.6	.67	35.6

**p *values calculated using chi-square and *t*-tests.

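### One of the two planned arm comparisons, the modified t-test, in its usual form uses no baseline value, and no stated analysis uses the baseline record-audit score already held; the cost is precision, not validity

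*Protocol article*

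**What the plan says.** The Data analysis section of the protocol article gives the method for comparing arms in one sentence: "To compare intervention effects between control and intervention groups, we will use adjusted, generalised linear models and modified" t-tests, taking the effect size into account. The word for adjustment is attached to the models, and no covariates are listed. The next sentence adds: "Analyses will be conducted at the cluster and individual level, and all estimates will be presented with standard deviations or 95% confidence intervals". Neither method is named as the leading one.

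The outcome to be compared is a provider-level score built from procedure codes in the electronic dental record (EDR). The Primary outcome measures section says: "When multiplying the procedure codes by the estimated ORs and summing the results, we will create one continuous primary outcome".

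The same source is read before the intervention. Under Trial design: "we will conduct a provider baseline survey and EDR audit to measure the baseline adherence to TUPAC counselling guidelines". Under Trial update, the baseline survey and "the EDR audit of the sample were conducted in September 2009". The stated purposes of that audit are to describe baseline adherence and, with the survey, to inform the design of the interventions. No section gives it a role in the comparison of arms, and none rules one out.

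**The concern.** A provider's own earlier score on the primary outcome is usually among the best predictors of the later score. Providers differ in how much they counsel and, as the Discussion concedes, in whether they enter the codes at all. Where those habits persist, an analysis without the baseline score leaves them in the error term.

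This trial has little precision to spare. It plans 12 clusters over three arms, allocated by drawing lots with no balancing described, and the Discussion itself calls the sample relatively small. If the modified t-test is reported as an effect analysis on a par with the model, one of the two headline intervals is likely to be wider than the data in hand require. The two analyses may also disagree, and nothing says which prevails.

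**Working it through.** **Inputs from the protocol article (Sample size).** 72 participants, 12 clusters, six per cluster on average; intra-class correlation 0.02; three arms. The layout is consistent: 12 × 6 = 72, and 72 / 0.76 = 94.7, which gives the 95 to be invited. The document gives no figure for the precision of the t-test, so there is none to reproduce on this point.

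**Assumptions.** Equal allocation, so 4 clusters and 24 providers per arm (no ratio is stated). The intra-class correlation of 0.02 applies to the score at both times. The provider-level correlation between baseline and follow-up score, rho, is not in the document, so a range is shown.

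**Step 1: design effect.** 1 + (6 − 1) × 0.02 = 1.10.

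**Step 2: large-sample effect of adjustment.** Interval width is multiplied by √(1 − rho²):
- rho 0.3: √0.91 = 0.95
- rho 0.5: √0.75 = 0.87
- rho 0.7: √0.51 = 0.71

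**Step 3: does this survive with so few clusters?** The analysis was simulated with 4,000 runs per value of rho. In stage one, the follow-up score is regressed on the provider's own baseline score with arm in the model. In stage two, the cluster means of the adjusted scores are compared between two arms with a t-test on 4 + 4 − 2 = 6 degrees of freedom. The comparator is the same t-test on unadjusted cluster means.

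| rho | Width, adjusted / unadjusted | Narrower by |
|---|---|---|
| 0 | 0.99 | about 1% (in effect unchanged) |
| 0.3 | 0.95 | 5% |
| 0.5 | 0.86 | 14% |
| 0.7 | 0.71 | 29% |

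Type I error was about 5% (range roughly 4% to 6%) with either method.

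**Step 4: the level of the covariate matters.** If the baseline were instead entered as a cluster-level covariate, a cluster degree of freedom would be lost. With an allowance for covariate imbalance in small samples, the width ratio at rho 0.3 becomes 1.04 with 12 clusters pooled (9 to 8 degrees of freedom) and 1.12 with 8 clusters in a pairwise comparison (6 to 5). At rho 0.7 it is 0.78 and 0.84. Those penalties do not apply in step 3, because the slope is estimated across about 72 providers and the cluster degrees of freedom are kept.

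**Step 5: the same variance seen as imbalance.** The standard deviation (SD) of the chance baseline difference between two arms is √(2 × 1.10 / 24) = 0.30 provider SDs. The typical part carried into an unadjusted effect is rho × 0.30: about 0.09, 0.15 and 0.21 SD at rho 0.3, 0.5 and 0.7. This is part of the variance already counted in steps 2 and 3, not an addition to it.

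**The case against.** The strongest reply is that the plan already commits to adjusted models. The article does not list their covariates, and an article may leave that list to the full plan. The baseline audit is an obvious candidate. That stands: a reader might infer that no analysis in this trial will use the baseline score, and the document does not support that. It shows only that none is stated to do so.

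It can also be said that the modification of the t-test is undefined, so change scores or adjusted summaries are not excluded. That is true, but a t-test modified for clustering in its usual form holds no covariate, and the word adjusted is not attached to it.

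An unadjusted test beside an adjusted one is not an error. That stands too, and the remedy keeps the unadjusted test in a lesser role.

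Two stronger readings should be resisted:
- **Bias.** A reader might infer that chance baseline imbalance biases the effect. Under randomisation it is sampling variability, and a valid clustered interval already includes it.
- **Power.** A reader might apply the variance reduction to the Sample size figures ("increase the proportion of counselled patients from 10.5% (control) to 33% in the first (low-intensity) intervention group") and quote a gain from 47% to 58% or 75% by the normal approximation at rho 0.5 or 0.7. Those figures are proportions of patients, while the t-test would analyse a continuous provider score, so such numbers are illustrative at best. Whether 72 participants suffice is a separate question.

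Finally, rho could be low. Sparse and under-recorded baseline codes may predict follow-up poorly, and the document does not settle this.

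**Conclusion.** The point holds for the modified t-test. It is one of two unranked arm comparisons, in its usual form it ignores a baseline measure of the outcome that is already held, and a better version needs no new data. Whether the generalised linear models share the weakness cannot be told from the article.

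The consequence is lost precision, not an invalid test. The loss is small at rho 0.3 and material from about 0.5 upwards. It rests on an assumed rho, equal arms of 4 clusters and the plan's intra-class correlation. Because the provider-level adjustment loses nothing in the simulation even at rho 0, the change should be made without knowing rho, with medium confidence that the gain will be material.

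**What to change.** In the Data analysis section:
1. Regress each provider's follow-up EDR score on that provider's own baseline EDR score, built from the same codes with the same scoring, with arm in the model.
2. Run the clustered t-test on the cluster means of the baseline-adjusted scores. Keep the covariate at provider level, not cluster level.
3. Name the same baseline score as a covariate in the generalised linear model.
4. Keep the unadjusted modified t-test as a sensitivity analysis, which also settles its rank.

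The cost is one or two sentences, with no new data, staff or participants. The downside is one estimated slope and a rule, fixed in advance, for a provider with no baseline record, for example cluster-mean imputation with an indicator.
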